## Abstract

**Purpose:**

Despite evidence of myocardial infarct size reduction in animal studies, remote ischaemic conditioning (RIC) failed to improve clinical outcomes in the large CONDI-2/ERIC-PPCI trial. Potential reasons include that the predominantly low-risk study participants all received timely optimal reperfusion therapy by primary percutaneous coronary intervention (PPCI). Whether RIC can improve clinical outcomes in higher-risk STEMI patients in environments with poor access to early reperfusion or PPCI will be investigated in the RIC-AFRICA trial.

**Methods:**

The RIC-AFRICA study is a sub-Saharan African multi-centre, randomized, double-blind, sham-controlled clinical trial designed to test the impact of RIC on the composite endpoint of 30-day mortality and heart failure in 1200 adult STEMI patients without access to PPCI. Randomized participants will be stratified by whether or not they receive thrombolytic therapy within 12 h or arrive outside the thrombolytic window (12–24 h). Participants will receive either RIC (four 5-min cycles of inflation [20 mmHg above systolic blood pressure] and deflation of an automated blood pressure cuff placed on the upper arm) or sham control (similar protocol but with low-pressure inflation of 20 mmHg and deflation) within 1 h of thrombolysis and applied daily for the next 2 days. STEMI patients arriving greater than 24 h after chest pain but within 72 h will be recruited to participate in a concurrently running independent observational arm.

**Conclusion:**

The RIC-AFRICA trial will determine whether RIC can reduce rates of death and heart failure in higher-risk sub-optimally reperfused STEMI patients, thereby providing a low-cost, non-invasive therapy for improving health outcomes.

## Introduction

Acute myocardial infarction (AMI) and the heart failure (HF) that often follows are among the leading causes of death and disability in sub-Saharan Africa (SSA) and worldwide [1]. The prevalence of ischaemic heart disease and its related mortality rate is predicted to rise by 70% in African men and 74% in women by 2030, and the burden of acute coronary syndromes in sub-Saharan Africa are steadily rising [2, 3]. Observational studies in sub-Saharan Africa have reported high in-patient mortality rates in STEMI patients ranging from 15 to 21%, with unacceptably high post-myocardial infarction (MI) heart failure rates [1, 2].

In most high-income countries, patients presenting with an acute ST-segment elevation myocardial infarction (STEMI) undergo immediate revascularization by primary percutaneous coronary intervention (PPCI) as the treatment of choice. However, in many low-and middle-income countries in sub-Saharan Africa, the availability and access to modern, expensive infrastructure and interventions such as PPCI are limited, and this is unlikely to change in the near future. As a result, of the STEMI patients who receive reperfusion, the majority are treated by thrombolysis and are more likely to develop heart failure and death post-STEMI, highlighting a higher-risk patient population. As such, there remains an urgent unmet need to discover novel therapeutic interventions that will improve clinical outcomes and prevent the onset of heart failure following STEMI.

In this regard, remote ischaemic conditioning (RIC), an endogenous cardioprotective phenomenon in which brief cycles of sublethal ischaemia and reperfusion applied to the limb, has been shown to reduce MI size in small and large animal models of acute myocardial ischaemia/reperfusion injury [4]. Crucially, the cardioprotective stimulus of RIC can be induced by simply inflating and deflating a pneumatic cuff placed on the upper arm or thigh for four 5-min cycles as adjunctive therapy in STEMI patients, making RIC an attractive low-cost and non-invasive treatment strategy for improving clinical outcomes in STEMI patients [5–10]. Although several clinical studies of STEMI patients reported reduced MI size with RIC, the large European CONDI-2/ERIC-PPCI multi-centre, randomized, clinical trial did not find any improvement in clinical outcomes [11]. Potential reasons for this failure to translate RIC into patient benefit included the low-risk population recruited into that study and the fact that patients who had received optimal reperfusion therapy by PPCI contributed to an unexpectedly low event rate in the sham treatment group, resulting in an unpowered trial [12–14]. In the RIC-AFRICA trial, we investigate whether RIC can improve clinical outcomes in higher-risk STEMI patients in sub-Saharan Africa treated by thrombolysis.

## Methods

### Study Design

The RIC-AFRICA study is a sub-Saharan African prospective, multi-centre, randomized, phase 3 double-blinded, sham-controlled clinical trial of 1200 STEMI patients across 20 sites in South Africa, Kenya, Sudan, and Uganda. Patients who are ineligible because they present after 24 h will be concurrently recruited into an independent observational arm of the study if they are within 72 h of MI onset. The study will be conducted in accordance with the Declaration of Helsinki and has received approval from the ethics committee of the University of Cape Town (September 10, 2021/ HREC107.2021). Trial enrolment will begin from December 01, 2021, and extend over a 24-month period. The RIC-AFRICA study protocol has been registered at www.clinicaltrials.gov (identifier: NCT04813159), and the study will be conducted and reported according to the CONSORT statement [15]. An independent data and safety monitoring board has been selected to oversee the trial. All participants will provide informed written consent.

### Study Population

We will be recruiting 3 different strata of STEMI patients.Adult patients (≥ 18 years old) presenting with STEMI receiving thrombolytic therapy within guideline-recommended time (i.e., within ±12 hours of most severe chest pain)Adult patients (≥ 18 years old) presenting with STEMI who are ineligible for thrombolysis because they present outside of guideline-recommended time (± 12 h) but within 24 h of most severe chest painAdult patients (≥ 18 years old) presenting with evidence of STEMI who do not receive thrombolysis and who present ≥ 24 h and within 72 h of most severe chest pain

### Interventional Arm: Randomized Control Trial

Patients who are deemed eligible for randomization into the trial on account of presentation with STEMI within 24 h will be eligible for the interventional arm of the study if the following inclusion/exclusion criteria are met.

#### Inclusion Criteria

I.Adult patients (≥ 18 years old) presenting with suspected STEMI (new ST-elevation at the J-point in two contiguous leads with the cut-points: ≥ 0.1mV in all leads other than V2-3 where the following cut-points apply: ≥0.2mV in men ≥40 years (≥0.25 mV in men <40 years) or ≥ 0.15mV in women)II.Within 24 h of onset of myocardial infarction as deemed by the attending clinicianIII.Signed informed consent

#### Exclusion Criteria

I.STEMI patients undergoing primary percutaneous coronary interventionII.STEMI patients presenting with cardiogenic shock or haemodynamic instability (systolic blood pressure (SBP) < 90 mmHg for ≥ 30 min, or use of pharmacological and/or mechanical support to maintain SBP ≥ 90 mmHg, and evidence of end-organ damage such as urine output of < 30 mL/h, altered mental status, and/or serum lactate > 2.0 mmol/L) [16]III.Contra-indication to thrombolytic therapy in patients presenting within guideline-recommended time (± 12 h)IV.Conditions that preclude the use of RIC or sham-control on either arm such as:Severe active skin disease/burns on both armsBilateral upper limb amputationsEvidence of acute limb ischaemia on either armActive upper limb gangrene of any digitsBilateral arteriovenous fistulae needed for haemodialysisKnown breast cancer with ipsilateral lymph node involvement on the side of RICV.Inter-current disease with an expected life expectancy of less than 24 h

### Observational Arm

There is currently very limited data surrounding late STEMI presentation, management, and outcomes across Africa where the condition is thought to be common. As this will be one of the first large scale interventional STEMI trials conducted across Africa, we have decided to use this opportunity to gather as much information as possible about patients who present with late STEMI to help narrow the gap on this subject in the medical literature, while concurrently generating future research opportunities in Africa. The participants in the observational arm will not be compared to the participants randomized to the trial intervention.

Patients who are deemed ineligible for randomization into the clinical trial on account of presentation beyond 24 h will be eligible for the observational arm of the study if the following inclusion/exclusion criteria are met.

#### Inclusion Criteria

I.Signed informed consentII.Adult patients (≥ 18 years old) with clinical evidence of STEMI older than 24 h and less than 72 h as defined by the following:Compatible history with maximal chest pain between 24 and 72 h prior to presentationCompatible biomarkers (elevated cardiac troponin)ECG compatible with recent STEMI; and/orCompatible echocardiography

#### Exclusion Criteria

I.Refusal or inability to sign informed consent

### Randomization

Consenting participants who present within 24 h of MI onset will be randomized to receive either RIC or sham control. Randomization will be conducted via an automated, secure web-based program built into the data capturing software. Randomization will be stratified according to recruiting site and time of MI-onset, using random permuted blocks. The randomization schedule will be conducted in a manner that ensures that 2 participants in stratum 1 (receives thrombolysis within ± 12 h of MI onset) are recruited for every participant in stratum 2 (outside the thrombolytic window but within 24 h of MI onset) and will ensure equal allocation to both the active and sham control arms. The patient, treating clinician, and study investigators will be blinded to the treatment allocation. Willing participants who present between 24 and 72 h of MI onset will be recruited into the concurrently running independent observational arm of the RIC-AFRICA study.

### Trial Intervention

An automated pneumatic blood pressure device (manufactured by Seagull Aps in Denmark) will be used to deliver either the RIC or sham protocol. The RIC protocol will comprise of applying the blood pressure cuff at recruitment on the upper arm to automatically deliver four 5-min alternating high-pressure cuff inflations (20 mmHg above each participant’s systolic blood pressure) and cuff deflations, such that the total RIC protocol takes 40 min. The sham control protocol will comprise the application of a visually identical pneumatic cuff on the upper arm which will automatically deliver four 5-min alternating low-pressure cuff inflations (20 mmHg) and cuff deflations, for a total of 40 min. The RIC and sham protocol will be repeated daily over the next two days. Enrolled participants in stratum 1 will receive RIC or sham control within 1 h of thrombolysis. Participants in stratum 2 will receive RIC or sham control within 1 h of randomization. The RIC and sham devices will be applied by the unblinded research nurse. None of the study interventions or procedures will interfere with standard STEMI management at each site. Participants enrolled in the observational arm will not receive any trial intervention.

### Study Endpoints

#### Primary Endpoint

For the purpose of this trial, all endpoints were consistent with the 2017 cardiovascular and stroke endpoint definitions for clinical trials consensus document [17].

The primary composite endpoints of the study will be all-cause death and early post-MI heart failure. The latter is defined as (a) pre-discharge (in-hospital) heart failure or (b) heart failure hospitalization within 30 days of discharge from index myocardial infarction (see Table 1 of Appendix for more details).

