### Statistical Analysis

All efficacy endpoints will be analysed according to the intention-to-treat principle. The primary analysis will be a comparison of all-cause death and post-MI heart failure hospitalization event rates at 30 days after randomization between the RIC and sham control arms in all randomized STEMI participants. Differences in means among the randomized groups will be analysed using the analysis of variance (ANOVA) test and, if required, the Turkey post hoc test, and differences in proportions using the χtest, or Fisher exact test, as appropriate. Follow-up will be measured from date of randomization until date of occurrence of the composite event (death or heart failure for primary analysis, and death, non-fatal MI, transient ischaemic attack or stroke, or HF with or without hospitalization for the secondary analysis) or end of the study. The primary outcomes will also be analysed in prespecified subgroups defined in our statistical analysis plan. Survival curves of study groups will be compared using the Kaplan-Meier method, and significance will be assessed using the Log-rank test. Cox proportional hazards regression models will be fitted to identify factors associated with the hazard of occurrence of the composite event. Strength of association will be expressed as a hazard ratio, with 95% confidence intervals and Wald test *p* value. All tests will be two-sided, and a *p* value < 0.05 will be considered significant. The Stata (TX, USA) statistical software will be used for data analysis.

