## Appendix

**Table 1. Tab1:** Definition of study endpoints according to the 2017 cardiovascular and stroke endpoint definitions for clinical trials [17]

Pre-discharge heart failure	I. New or worsening symptoms of heart failure (dyspnoea, decreased exercise tolerance, fatigue, or symptoms of worsened end-organ perfusion or volume overload) II. Objective clinical evidence of heart failure and fluid retention (such as pulmonary crepitations/crackles, raised JVP, S3 gallop, peripheral oedema, increasing abdominal distension/ ascites, or rapid weight gain thought to be related to fluid retention) III. Radiological evidence of pulmonary congestion/ oedema IV. Increased cardiac biomarkers (such as BNP > 500 pg/mL or NT-proBNP > 2,000 pg/mL) V. The initiation of intravenous or the significant augmentation of oral loop diuretic therapy
Heart failure hospitalization at 30 days	I. An admission ≥ 24 h II. A diagnosis of heart failure made by the treating clinician III. The initiation of intravenous or the significant augmentation of oral loop diuretic therapy
Non-fatal myocardial infarction	Acute re-infarction MI that occurs in the first 28 days after the index admission for STEMI, defined by [18]: I. Recurrent ischaemic symptoms II. New ST segment deviation in at least two contiguous leads III. A ≥ 20% increase between an immediate cTn value taken at re-admission and a subsequent cTn value taken 3–6 h later, exceeding the 99th percentile upper range limit
Transient ischaemic attack	A transient episode of focal neurological dysfunction caused by brain, spinal cord or retinal ischemia, without acute infarction
Stroke	An acute episode of focal or global neurological dysfunction caused by brain, spinal cord, or retinal vascular injury as a result of haemorrhage or infarction
Heart failure without hospitalization	An event that meets the clinical criteria for heart failure but does not meet the length-of-hospital stay, i.e. an admission < 24 h

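### The heart failure hospitalization component runs to 30 days after discharge, but the primary analysis counts events to 30 days after randomization, so later readmissions count under one text and not the other

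*Protocol article*

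**What the plan says.** All references are to the Protocol article.

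- **Primary Endpoint** (Methods, Study Endpoints): the composite is death from any cause plus early heart failure after the infarction. Heart failure has two parts: (a) in hospital before discharge, and (b) "heart failure hospitalization within 30 days of discharge from index myocardial infarction". No window is attached to death here.
- **Statistical Analysis**, primary analysis: a comparison of "event rates at 30 days after randomization between the RIC and sham control arms".
- **Statistical Analysis**, time-to-event follow-up: "Follow-up will be measured from date of randomization until date of occurrence of the composite event". The sentence names both the primary and the secondary composite and closes "or HF with or without hospitalization for the secondary analysis) or end of the study". It states no day-30 cap, and the article does not define the end of the study.
- **Abstract, Methods**: "composite endpoint of 30-day mortality and heart failure", with no starting point for the 30 days.
- **Appendix, Table 1**: "Heart failure hospitalization at 30 days", again with no starting point.
- **Sample Size Determination**: an audit gave 14% mortality and 18% readmission with heart failure at 30 days. The planning rate is 30%. The article does not say whether the audit's 30 days ran from admission or from discharge.

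**The concern.** The definition and the primary analysis govern the same composite but stop counting on different days. A readmission on day 34 after a 6-day stay is day 28 after discharge. It is a primary event under the definition and a non-event under the analysis. Whoever adjudicates or programs the endpoint must override one text to follow the other, and the article gives no rule for choosing.

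The discharge clock has a second weakness. Discharge happens after randomization, and in-hospital heart failure, itself part of the endpoint, can be expected to affect length of stay. A window of stay plus 30 days therefore differs between patients. It would also differ between arms if the intervention changed the stay. A fixed window from randomization avoids this.

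At stake is which late readmissions enter the primary result. A choice between the two texts that is still open when data are seen is best removed beforehand.

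**Working it through.** **1. The plan's own figure.** Inputs from Sample Size Determination: control rate 30%; 25% relative reduction, so 0.75 × 30% = 22.5%; 80% power; 5% significance. Statistical Analysis makes tests two-sided, and Randomization gives equal allocation. The two-proportion formula with pooled variance under the null is

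n per arm = [1.960·√(2p̄(1−p̄)) + 0.842·√(p₁(1−p₁) + p₂(1−p₂))]² / (p₁−p₂)², with p̄ = 0.2625.

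It gives 539.1 per arm, which is 1078 rounded down or 1080 rounded up. Power at 539 per arm is 80.0%. For drop-out, 1078/0.9 = 1198, rounded to 1200. The stated sample size reproduces.

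**2. The two windows.** Let L be the index stay in days, and take randomization as the day of admission (an assumption). The analysis stops at day 30. The definition's heart failure hospitalization component stops at day L + 30. They agree only at L = 0. The article gives no length of stay, so the values of L below are assumptions.

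**3. How many readmissions fall between the windows.** Assume the audit's 18% was counted over 30 days from discharge, with a constant hazard:

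λ = −ln(1 − 0.18)/30 = 0.00662 per day.

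Readmissions by day 30 from randomization = 1 − exp(−λ(30 − L)).

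| L (days) | Definition ends | Readmitted by day 30 | After day 30 (points) | Share of the 18% |
|---|---|---|---|---|
| 3 | day 33 | 16.4% | 1.6 | 9% |
| 5 | day 35 | 15.2% | 2.8 | 15% |
| 7 | day 37 | 14.1% | 3.9 | 22% |
| 10 | day 40 | 12.4% | 5.6 | 31% |
| 14 | day 44 | 10.0% | 8.0 | 44% |

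A simple uniform share, L/30, gives nearly the same: 17% at 5 days and 33% at 10 days.

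**4. Conditional effect on power.** Suppose also that every late readmission removes one composite event. The rest of the planning rate is 30% − 18% = 12%. Then, at 539 per arm and the same 25% relative reduction:

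- L = 5: constant hazard 12% + 15.2% = 27.2%, power 74.7%. Uniform share 12% + 15% = 27.0%, power 74.2%.
- L = 10: constant hazard 12% + 12.4% = 24.4%, power 68.6%. Uniform share 12% + 12% = 24.0%, power 67.7%.

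This step leaves out two things, and both make the loss look larger than it would be. Pre-discharge heart failure is in the composite but not in the sum. It adds events, and a patient who had it is already counted whatever happens later. The audit components also overlap: 14% + 18% = 32% against the 30% used, so about 2 points of patients may have both events, and some of them would still count through death.

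**The case against.** The best defence is that the Statistical Analysis section already names an anchor and a day for the primary analysis. On that text every patient has the same 30-day window, and unequal windows arise only if the endpoint definition is allowed to override it. This stands as a limit on the harm. It does not remove the conflict: the definition says which hospitalizations qualify, and nothing in the article says that the analysis text prevails. Nor is this detail left to a fuller document, because the article itself states two incompatible windows.

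Four stronger readings are tempting, and the document does not support them.

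- **The end of the study as a third primary window.** A reader might infer follow-up of very different lengths across the 24-month recruitment. But the phrase belongs to the follow-up for the Kaplan-Meier, log-rank and Cox analyses, and the primary analysis is stated separately. Every other stated horizon is 30 days and no later visit is described, so it may simply mean the end of each patient's 30-day follow-up. It is loose wording that needs a cap.
- **An established loss of power.** This requires the audit's 18% to be counted from discharge, and the article does not say so. If it was counted from admission, the 30% rate already roughly matches the analysis clock and little or no power is lost.
- **Patients who die in hospital have no defined window.** True of the discharge clock, but harmless: they already have a primary event.
- **Demonstrated bias between arms.** The article gives no data on whether the intervention changes length of stay. Dependence on a post-randomization variable is a reason to avoid the discharge clock. It is not evidence of bias of any given size.

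**Conclusion.** The point holds as a contradiction between the endpoint definition and the primary analysis, and it rests on the article's wording alone. Its reach is the set of readmissions after day 30 from randomization but within 30 days of discharge. With assumed stays of 3 to 14 days that is about 1.6 to 8.0 percentage points of readmission, given an 18% rate counted from discharge, a constant hazard and randomization at admission.

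The sample size is correct as computed. Power of about 75% (5-day stay) to 68–69% (10-day stay) is an upper-end illustration that depends on an unstated audit clock and ignores pre-discharge heart failure and overlap with death. It should not be reported as a finding about this trial's power. The missing day-30 cap on time-to-event follow-up is a lesser, related point. Because the conflict decides which events enter the primary result, it should be settled before unblinding.

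**What to change.** - In Primary Endpoint, change part (b) so that heart failure hospitalization is counted within 30 days of randomization. State the same window for death and for pre-discharge heart failure, so that every component runs from randomization to day 30 in every patient.
- In Statistical Analysis, censor the Kaplan-Meier, log-rank and Cox analyses at day 30 in place of the undefined end of the study. Give the same starting point in the Abstract and in Appendix Table 1.
- In Sample Size Determination, state whether the audit's 18% and the 30% planning rate run from admission or from discharge.
- If readmission within 30 days of discharge is of interest, report it as a secondary measure.

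The change to the endpoint and analysis is wording only. The cost is that slightly fewer late readmissions count. If the audit proves to be discharge-based, the planning rate or the stated power should be restated on the randomization clock. On the illustrative rates above (27.2% and 24.4%), the same formula would need about 1,228 to 1,416 patients before drop-out for 80% power, against 1,078. If the audit was counted from admission, the stated figure can stay.
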